##### 11.3.1.2 Events Meeting the Adverse Events Definition

- Any abnormal laboratory test results (hematology, clinical chemistry, or urinalysis) or other safety assessments (e.g., ECG, radiological scans, vital signs measurements), including those that worsen from baseline, considered clinically significant in the medical and scientific judgment of the investigator (i.e., not related to progression of underlying disease);
- Exacerbation of a chronic or intermittent pre-existing condition including either an increase in frequency and/or intensity of the condition;
- New conditions detected or diagnosed after the participant has signed the consent form, though it may have been present before the start of the study;
- Signs, symptoms, or the clinical sequelae of a suspected drug-drug interaction;

- Signs, symptoms, or the clinical sequelae of a suspected overdose of either study treatment or a concomitant medication. [REDACTED]

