#### **11.3.1.5 Treatment-Emergent Adverse Event**

TEAEs are defined as any AE occurring or worsening on or after the first dose of study treatment.

[figure not shown]

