### **11.3.4 Recording of Adverse Events and Serious Adverse Events**

Any AE is to be recorded starting immediately after the participant provides informed consent through the end of the safety follow-up period (or until withdrawal from the study, whichever is later).

When an AE/SAE occurs, it is the responsibility of the investigator to review all documentation (e.g., hospital progress notes, laboratory reports, and diagnostics reports) related to the event. The investigator will then record all relevant AE/SAE information in the eCRF. It is not acceptable for the investigator to send photocopies of the participant's medical records in lieu of completion of the AE/SAE eCRF page. There may be instances when copies of medical records for certain cases are requested. In this case, all participant identifiers, with the exception of the study participant number, will be redacted on the copies of the medical records before submission. The investigator will attempt to establish a diagnosis of the event based on signs, symptoms, and/or other clinical information. Whenever possible, the diagnosis (not the individual signs/symptoms) will be documented as the AE/SAE.

The following variables will be recorded for each AE: verbatim/AE description and date for AE start and stop, intensity (Section 11.3.4.1), seriousness (Section 11.3.1.4), causality rating (Section 11.3.4.2), whether or not the AE caused the participant to discontinue (Section 9.4), any other action (Section 11.3.4.3). Continuous events should be recorded at the maximum severity observed.

Expedited reporting, as described in Section 11.3.6, is required for SAEs, but not required for nonserious AEs or laboratory abnormalities.

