### Visit Windows for Safety Laboratory Testing (hematology and chemistry) and ESR

| Nominal Week | Nominal Study Day | Visit Window                                          |
|--------------|-------------------|-------------------------------------------------------|
| 0            | 1                 | All assessments prior to the start of study treatment |
| 4            | 29                | Day 2 – 43                                            |
| 8            | 57                | Day 44 – 71                                           |
| 12           | 85                | Day 72 - 99                                           |
| 16           | 113               | Day 100 - 127                                         |
| 20           | 141               | Day 128 - 155                                         |

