## 8.9.1 Adverse Events

All AEs will be classified by Primary SOC and PT according to MedDRA Version 25.0 or higher and will be graded according to the National Cancer Institute Common Terminology Criteria for Adverse Events (NCI CTCAE) version 5.0.

AEs will be summarized by SOC and PT using counts and percentage (i.e., number and percentage of participants with an AE). AEs will be sorted by decreasing frequency within each SOC and PT as per the overall column.

Where a participant has the same AE, based on PT reported multiple times, the participant will only be counted once at that PT level. Where a participant has multiple AEs within the same SOC, the participant will only be counted once at that SOC level.

If a participant experiences the same AE more than once with different severity grades, then the event with the highest severity will be tabulated by maximum severity. In addition, AEs with a missing severity will be presented in the summary table under the category of ‘Missing’ and will not be imputed.

TEAEs are defined as any AE occurring or worsening on or after the first dose of study treatment.

TEAEs will be assigned to Part A, Part B and Part A+B using the event start date and time and will be defined as:

- Part A: events started on or after the first dose of study medication for Part A but not after Part B or events present prior to the first dose of study medication for Part A but increased in severity on or after dosing on Part A but not after Part B
- Part B: events started on or after the first dose of study medication for Part B or events present prior to the first dose of study medication for Part B but increased in severity on or after dosing on Part B

For Part A+B treatment emergent AEs relating to the Part when the subject was on the corresponding treatment are considered as TEAE.

Adverse events with an onset on Day 1 which are based upon pre-dose lab tests will be considered as not treatment emergent. These are defined as:

- Adverse events which begin on study day 1 with SOC = “Investigations” or PT in (“Hypercholesterolaemia” “Hyperlipidaemia” “Dyslipidaemia”, “Type V hyperlipidaemia”).
- The latest lab test taken on Day 1 has a time which is before the treatment start time.

Treatment-related AEs are those events with relationship to study drug ‘Related’ as recorded on the CRF. If the relationship to study drug is missing, the AE will be considered as treatment related.

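### The SAP's Day 1 exclusion for pre-dose laboratory AEs relies on organ class and an unlinked laboratory time, so it can misclassify treatment-emergent status in both directions

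*Combined protocol and SAP*

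**What the plan says.** Protocol 11.3.1.5, repeated in SAP 8.9.1, gives the general definition: "TEAEs are defined as any AE occurring or worsening on or after the first dose of study treatment". Protocol 11.3.2 adds that whatever is observed before the first dose is recorded but kept apart from the TEAEs, without regard to organ class.

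SAP 8.9.1 then adds a Day 1 rule with a stated aim: "Adverse events with an onset on Day 1 which are based upon pre-dose lab tests will be considered as not treatment emergent". Two bullets define these events:

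- The first begins "Adverse events which begin on study day 1 with SOC" and names Investigations, or alternatively four preferred terms: hypercholesterolaemia, hyperlipidaemia, dyslipidaemia and type V hyperlipidaemia.
- The second reads "The latest lab test taken on Day 1 has a time which is before the treatment start time".

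No AND or OR joins the bullets. I read them jointly, because the second describes the participant's laboratory record and cannot identify an event on its own.

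On timing, SAP 8.9.1 says "TEAEs will be assigned to Part A, Part B and Part A+B using the event start date and time". Protocol 11.3.4, listing what is captured for each AE, names only "verbatim/AE description and date for AE start and stop". SAP 7.3.2 imputes a missing AE start day to the first-dose date when month and year match and the event did not end before that date. SAP section 9 does not list the Day 1 rule among the changes from the protocol.

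**The concern.** The aim concerns the cause and timing of an event: did a pre-dose sample give rise to it? The definition uses a dictionary class and the time of a laboratory test that need have nothing to do with the event. Such a proxy can fail in two ways. It can take a genuine post-dose event out of the TEAE tables, and it can leave in them a finding that was present before treatment.

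TEAE status feeds the SAP 8.9.1 summaries (all TEAEs, Grade 3/4/5, maximum intensity, related, leading to discontinuation) and the exposure-adjusted rates, whose numerator is the number of participants with at least one event. Arms are small, at about 40 each.

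**Working it through.** No figure in the plan needs reproducing. The check applies the rule to cases.

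**Inputs**

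- General definition: treatment-emergent if onset or worsening is on or after first dose (protocol 11.3.1.5; SAP 8.9.1).
- Day 1 rule: not treatment-emergent if start is Day 1, and class is Investigations or the term is one of the four lipid terms, and the latest Day 1 laboratory time is before dosing (SAP 8.9.1).
- Day 1 laboratory tests: hematology, chemistry, urinalysis, ESR, hs-CRP, fasting lipids and glucose (Schedule of Activities, Week 0).
- Week 0 window for hematology and chemistry: "All assessments prior to the start of study treatment" (SAP 7.2).
- Assumptions: dose at 10:00; pre-dose samples at 09:00; a Day 1 event with no clock time counts as on or after first dose.

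**Comparator.** A laboratory-derived event takes the time of the sample that triggered it. Any other event takes its own onset time.

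| Day 1 case | SAP rule | Comparator |
|---|---|---|
| 1. Vital-sign finding coded to Investigations, onset 11:00 | not TEAE | TEAE |
| 2. As 1, date only | not TEAE | TEAE |
| 3. Pre-dose lab finding in Investigations, date only | not TEAE | not TEAE |
| 4. Pre-dose lab finding in another class, not a listed lipid term, date only | TEAE | not TEAE |
| 5. As 4, onset 09:00 recorded | not TEAE | not TEAE |
| 6. Pre-dose lab finding, listed lipid term, date only | not TEAE | not TEAE |
| 7. As 3, with a repeat lab test at 11:00 | TEAE | not TEAE |
| 8. Vital-sign finding coded outside Investigations, onset 11:00 | TEAE | TEAE |

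The two rules disagree in 4 of 8 cases: 1, 2, 4 and 7. The cases were chosen to probe the logic, so 4/8 is not an error rate.

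**Reading the disagreements**

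- Case 1 contradicts the general definition directly. A recorded post-dose onset does not help, because the Day 1 rule never consults it. Case 2 shows the same outcome with no clock time.
- Case 4 conflicts with protocol 11.3.2. Outside Investigations only lipid terms are covered, although several other kinds of test are done on Day 1. The lipid list itself shows that laboratory findings can be coded outside Investigations.
- Case 7 arises because the second bullet uses the latest Day 1 test rather than the one behind the event.

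**Imputed dates.** Take an event coded to Investigations with its start day missing and its month equal to the first-dose month. SAP 7.3.2 sets its start to Day 1, which makes it treatment-emergent. If that participant's Day 1 tests were all pre-dose, the Day 1 rule then reverses this, although the event may have begun at any later point in the month.

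**Size of one misclassification.** 1/40 = 2.5 percentage points in an arm of 40, provided the participant has no other event in the same table row.

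**The case against.** The best defence is that the Day 1 bullets add to the general rule and do not replace it. A pre-dose finding with a recorded pre-dose time is already excluded by protocol 11.3.2 and by the use of start date and time in SAP 8.9.1, as case 5 shows. This stands. The second failure therefore needs a missing clock time, which is plausible because protocol 11.3.4 names only a date.

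The second bullet also does some work: a sample drawn after dosing, for instance to investigate a reaction, switches the exclusion off. Pre-dose collection is stated expressly for ADA and PK samples (protocol 11.6, 11.7) but not, in the visible text, for safety laboratory tests. The SAP 7.2 window is an analysis window and not a sampling instruction.

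The consequence is limited. Affected events remain recorded. SAEs, fatal AEs and AESIs are summarized without a TEAE label. The general definition still counts an event that worsens after dosing, and no formal safety testing is planned.

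A reader might infer more than the documents support:

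- *That the rule takes no account of when an event began.* It does require a start on Day 1; what it ignores is the time of day.
- *That first-dose reactions, including ECG abnormalities, are lost as a class.* No ECG is scheduled on Day 1, so one would have to be unscheduled. Vital signs are scheduled then, but the visible text gives no timing relative to dosing, and neither document says which vital-sign terms code to Investigations. The vital-sign cases above depend on that coding.
- *That practically all such post-dose events are removed and no pre-dose findings outside the listed terms are.* Neither rate can be derived, since sampling times and the completeness of onset times are not given.

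None of this reconciles the stated aim with the definition that carries it out.

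**Conclusion.** The rule is wrong as written, and the point is minor. Followed literally, SAP 8.9.1 can remove TEAE status from a non-laboratory Investigations event that began after dosing on Day 1. It can also leave as TEAEs two kinds of date-only pre-dose finding: those outside Investigations and the four lipid terms, and those in Investigations when a later Day 1 test was post-dose. It can undo the start-day imputation in SAP 7.3.2 as well.

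The effect on the TEAE tables and exposure-adjusted rates is not quantified in the documents and is probably small. The 2.5-point figure is the arithmetic of one participant in 40, not an estimate of bias.

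The conclusion assumes that the two bullets apply jointly. Its first part needs all of a participant's Day 1 laboratory samples to be pre-dose and some non-laboratory events to be coded to Investigations. Its second part needs AEs recorded by date alone.

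**What to change.** Replace the two bullets in SAP 8.9.1 with a rule tied to the event:

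1. Where an onset time is recorded, classify the Day 1 AE by that time relative to the first dose.
2. Where none is recorded, class the AE as not treatment-emergent only if it is laboratory-derived, in any organ class, and the sample that triggered it was collected before the first dose. Identify these AEs from a list agreed in blinded medical review before database lock.
3. Treat every other Day 1 AE as a TEAE.
4. Do not apply the exclusion to a Day 1 date that was imputed under SAP 7.3.2.

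Applied to the eight cases, this gives the comparator's answer each time: case 1 changes under item 1, case 2 under item 3, and cases 4 and 7 under item 2. Worsening after dosing stays governed by the general definition.

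The cost is a paragraph of SAP text, a small programming change and a short blinded review list. No new data are needed.

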### 8.9.2 Clinical Laboratory Evaluations

All central laboratory (hematology, biochemistry, urinalysis) parameters will be collected as described in [Appendix I](#).

Observed and change from baseline values for clinical laboratory parameters will be summarized using descriptive statistics by treatment group and visit separately for Part A and Part B. Shift from baseline to each scheduled assessment and the worst post treatment value according to normal ranges criteria will be presented. Shift from baseline to each scheduled assessment and the worst post treatment value according to CTCAEv5.0 criteria will also be presented. CTCAEv5.0 criteria are described in [Appendix L](#). Participants meeting any grade 3 criteria will also be listed.

In addition, the number and percentage of participants meeting the criteria for normal ranges in laboratory parameters will be summarized by treatment group separately for Part A and Part B.

Laboratory results together with the normal ranges will be listed, flagging values that are below or above the normal range. Serum/urine pregnancy tests assessments will be listed only.

Boxplots of the observed and change from baseline values for all clinical laboratory parameters will be presented by treatment group and visit for Part A and Part B. Reference lines for the normal ranges, that consistent across all participants being presented, will be displayed.

For participants with an AE of grade 3 or higher the hematology and chemistry lab parameters for that participant will be presented in a panel plot with a panel for each lab parameter. The x-axis will be the study week and the y-axis will be the absolute lab value.

### 8.9.3 Vital Signs

Vital sign parameters collected are weight (kg), systolic and diastolic blood pressure (SBP and DBP) (mmHg), heart rate (beats/min), respiratory rate (breaths/min) and temperature (°C).

Observed values and the corresponding change from baseline values will be summarized using descriptive statistics by treatment group and visit separately for Part A and Part B.

In addition, the number and percentage of participants meeting criteria for potentially clinically significant abnormalities in vital signs (SBP, DBP and heart rate) and body weight will be summarized by treatment group separately for Part A and Part B. The following table presents the Criteria for clinically relevant abnormalities.

**Table: Criteria for Clinically Relevant Abnormalities in Vital Sign Parameters**

| Parameter              | Criteria                                                                                                                    |
|------------------------|-----------------------------------------------------------------------------------------------------------------------------|
| SBP (mmHg)             | Value $\leq 90$ or decrease $\geq 20$ mmHg from baseline
Value $\geq 180$ or increase $\geq 20$ mmHg from baseline       |
| DBP (mmHg)             | Value $\leq 50$ or decrease $\geq 15$ mmHg
Value $\geq 105$ or increase $\geq 15$ mmHg                                   |
| Heart Rate (beats/min) | Value $\leq 50$ bpm or decrease from baseline $\geq 20$ bpm
Value $\geq 120$ bpm or increase from baseline $\geq 20$ bpm |
| Weight (kg)            | $\geq 7\%$ decrease from baseline
$\geq 7\%$ increase from baseline                                                      |

#### 8.9.4 Physical Examinations

The following parameters and body systems will be examined and any abnormalities described general appearance, skin (presence of rash), HEENT (head, ears, eyes, nose, throat), lungs (auscultation), heart (auscultation for presence of murmurs, gallops, rubs), lower extremity exam, abdomen (palpation and auscultation), neurologic (mental status, station, gait, reflexes, motor and sensory function, coordination) and lymph nodes.

All physical examination findings will be listed only.

#### 8.9.5 Electrocardiograms

The standard 12-lead ECG parameters collected are: intervals (RR, PR, QRS, QT and QT intervals corrected for heart rate using Bazett's and Fridericia's formulas [QTcB and QTcF, respectively]).

Observed values and the corresponding change from baseline values will be summarized using descriptive statistics at each scheduled assessment by treatment group separately for Part A and Part B.

The overall ECG interpretation will be summarized by presenting the number and percentage of participants with 'Normal' and 'Abnormal' by visit and treatment group for Part A and Part B. Shift tables from baseline (Normal/Abnormal) to each visit and to the worst post-baseline ECG interpretation will be summarized.

ECG data will be listed by participants at each visit and time point collected with indicated clinically significant results.

In addition, the number and percentage of participants meeting the criteria for potentially clinically significant abnormalities in ECG parameters will be summarized by treatment group separately for Part A and Part B. The following table presents the criteria for clinically relevant abnormalities.

**Table: Criteria for Clinically Relevant Abnormalities in ECG Parameters**

| Parameter     | Criteria                                                                                                                                                                                                 |
|---------------|----------------------------------------------------------------------------------------------------------------------------------------------------------------------------------------------------------|
| PR Interval   | >200 ms
>200 ms and increase from baseline $\geq 25\%$
> 220 ms
>220 ms and increase from baseline $\geq 25\%$
> 240 ms
> 240 ms and increase from baseline $\geq 25\%$                   |
| QRS Interval  | >110 ms
>110 msec and increase from baseline $\geq 25\%$
>120 ms >120 ms and increase from baseline $\geq 25\%$                                                                                    |
| QT Interval   | >500 ms                                                                                                                                                                                                  |
| QTcB and QTcF | Absolute Values
>450 to $\leq 480$ msec
>480 to $\leq 500$ msec
>500 msec
Change from baseline:
Change from baseline >30 to $\leq 60$ msec
Change from baseline >60 msec |

[figure not shown]

### **8.10 Subgroup Analysis**

Subgroup analyses for the primary endpoint and key secondary endpoints may be considered for the following baseline variables:

- Sex (male, female);
- Weight ( $< 100\text{kg}$ ,  $\geq 100\text{kg}$ );
- Prior exposure to biologic agents (yes/no);
- Concomitant DMARD use (yes/no)

These subgroup analyses will be carried out using the participants from FAS for Part A only.

Categorical variables will be analysed using a logistic regression model as per [Section 8.6.1.1](#) but with the addition of the subgroup and subgroup by treatment interaction as covariates.

A forest plot will be used to display the results of the subgroup analyses.

If an individual subgroup for a variable includes fewer than 5% of the total planned study size, the subgroup analyses for that variable may be omitted.

Additional subgroup analyses may be performed at the sponsor's discretion. These additional analyses are beyond the scope of this SAP and will be specified in a separate document, if needed.

Subgroup analysis will be done pairwise to match with the main analysis. A logistic regression model including fixed effects for treatment and stratification factors sex and exposure to biologic agents prior to the screening visit is used for the odds ratio and 95% CI. The adjusted risk difference and 95% confidence interval will be found in the same way as for the main analysis, calculated for each combination of treatments within each subgroup category.

## 8.11 Interim Analysis

Not applicable.

## 8.12 Primary Analysis Timing

The primary analysis and unblinding of the data will be performed when all data up to and including Week 12 has been collected and database lock declared.

The study will be continued regardless of the results of the primary analysis.

## 8.13 Data Safety Monitoring Board

As required, a select number of safety outputs will be generated for the review of the DSMB. For full details of the scope of the DSMB, please see the DSMB charter. In addition a summary of the observed ACR50 responders will be presented for FAS.

## 8.14 Development Safety Update Report

As required, the below DSUR summaries will be generated (until unblinding only a blinded column will be presented):

- Number of participants randomized;
- Number of participants exposed by age and sex;
- Number of participants exposed by race;
- Number of SAEs within the DSUR reporting period;
- Number of SAEs;
- Listing of SAEs.

